##### **Efficacy outcomes**

##### 

**Definition of outcome measures (including trial periods)** All secondary efficacy outcomes are defined separately at weeks 12, 24 and 52 unless specified otherwise (see Baseline and Outcome Measures). The PACE Scoring Protocol outlines in detail the process for calculating scores from questionnaire items and variables from case report forms. Participant-, therapist- and SSMC doctor-rated CGI are defined as ordinal variables with three categories. Participant satisfaction is defined as an ordinal variable with seven categories. The anxiety and depression subscale scores of the HADS, the Walking Test, and the total score of the Work and Social Adjustment scale are all continuous variables. However, the distribution of these is not pre-specified with the possibility that some or all may be skewed and the Walking Test may be bimodal. The number of CDC symptoms is a count variable and CDC Symptoms (1) and (8) are binary variables.

##### 

**Descriptive statistics for outcome measures** The distributions of all secondary efficacy outcomes will be presented in histograms (continuous/count) or bar charts (ordinal/binary) both overall and by intervention at each assessment point. A single table will be produced including summary statistics for all secondary efficacy outcomes by intervention and assessment point. Numbers (and percentages) or means (and standard deviations, minimums and maximums) or medians (and inter-quartile ranges, minimum and maximums) will be presented as appropriate. Summary statistics will be further plotted using line graphs for each outcome across time by intervention. The anticipated profiles have not been specified in advance. Potential variability in secondary efficacy outcomes between therapists and between doctors will be investigated using an approach similar to that outlined for the primary outcomes.

##### 

**Primary analysis (including method of analysis)** The primary analyses addressing secondary objective (3) will involve the secondary efficacy outcomes and will be based on the intention-to-treat principle. Participant will be included as a random intercept (investigating adding a random slope on time), time (investigating the possibility of linearising this effect across 12, 24 and 52 weeks) and the associated baseline variable as fixed effects and centre, CDC criteria, London criteria, and Current Depressive Disorder as fixed indicator variables. Participant-rated CGI and the participant satisfaction will be analysed using mixed-effects ordinal logistic regressions. The anxiety and depression subscale scores of the HADS, number of CDC symptoms, the Jenkins sleep scale total score, the Walking Test, and the total score of the Work and Social Adjustment scale will be analysed using mixed-effects linear regressions, unless there is evidence to suggest that these outcomes are skewed/bimodal, in which case transformation and bootstrapping will be investigated. CDC Symptoms (1) and (8) will be analysed using mixed-effects logistic regressions. The intervention and time-by-intervention contrasts fitted for the primary outcomes will be extracted for each secondary efficacy outcome as outlined in the analyses of the primary outcomes.

##### 

**Baseline adjustment** The same as that outlined for the primary outcomes

##### 

**Model assumptions checks** The following will be checked as described for the primary analysis of the primary outcomes

1. Independence of residuals

2. Distribution of residuals

3. Equal variance of residuals

4. Distribution of random effects (as appropriate)

5. Absence of an intervention-by-centre interaction

6. Extreme outliers and points with high leverage

##### 

**Other analyses supporting the primary analysis** Sensitivity analyses investigating the robustness of the conclusions of the primary analyses of the secondary efficacy outcomes will be less extensive than those described for the primary outcomes unless concern is raised by those carried out for the primary outcomes.

##### 

**Safety outcomes** These analyses will be based on the safety sample (see Trial Samples).

##### 

**Definition of outcome measures (including trial periods)** The safety of the trial interventions will be assessed using the definition of serious deterioration that was developed for monitoring safety during the course of the trial (see Outcome Measures), participant-rated adverse events defined and recorded in accordance with the protocol, and withdrawals from intervention. Serious deterioration, defined at 52 weeks, will be the primary assessment of safety. Its four components will be reported separately to enable evaluation of their relative contributions. These draw on the two adverse outcomes defined in the protocol, namely negative change on either the participant-rated CGI or the SF-36 physical function scale defined at 12, 24 and 52 weeks.

Participant-reported adverse events, including comorbid conditions which started after randomisation, are reported in terms of their relatedness to the trial intervention (events versus reactions), seriousness (non-serious versus serious) and severity (mild, moderate, severe). In addition serious adverse events are reported by the above and by their expectedness (expected versus unexpected).

Three independent assessors, initially blinded to intervention, selected by AfME and approved by the TSC, will do the following:

1. review all non-serious adverse events to determining if any should be upgraded to serious adverse events (SAEs) (masked to intervention);

2. review all SAEs to agree their classification as such (masked to intervention);

3. rate the relationship of each SAE to the randomised interventions (unmasked to intervention) (to consider whether any might be serious adverse reactions (SAR) to an intervention or suspected unexpected serious adverse reactions (SUSAR)); and

4. review all SARs and SUSARs.

Assessors will work independently of each other during the both classification periods. Where there is disagreement, consensus will be sought. Where disagreement continues, a majority vote will be taken.

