vi)	Serious deterioration: Component 3	Absent/present - Withdrawal from therapy more than 8 weeks after randomisation due to participant’s reported worsening of their condition
vii)	Serious deterioration: Component 4	Absent/present - A serious adverse reaction
viii)	Serious adverse events	Total number up to 52 weeks
ix)	Serious adverse reactions	Total number up to 52 weeks
x)	Adverse events	Total number and the proportion of participants having one or more up to 52 weeks
xi)	Withdrawals from intervention	No/yes; person responsible; reason; days from randomisation
xii)	Participant-rated CGI	Positive change; no change; negative change
xiii)	Anxiety (HADS-A)	Total (sum) of the anxiety items of the HADS (higher scores indicate more anxiety)
xiv)	Depression (HADS-D)	Total (sum) of the depression items of the HADS (higher scores indicate more depression)
xv)	Six minute walking test	Total number of meters walked - derived from the number of 10 meter lengths plus any partial distance
xvi)	Work and social adjustment	Total (sum) of all items (higher scores indicate less adjustment)
xvii)	Participant satisfaction	Very satisfied; moderately satisfied; slightly satisfied; neither; slightly dissatisfied; moderately dissatisfied; very dissatisfied
xviii)	CDC Symptoms (#)	Total (sum) of CDC symptoms 1 to 8
xix)	Jenkins Sleep Score	
xx)	CSRI - service costs	Total (sum) costs - derived by assigning costs (£) to each relevant item in the CSRI
xxi)	CSRI - societal costs	Total (sum) costs - derived by assigning costs (£) to each relevant item in the CSRI
xxii)	CSRI - NHS costs	Total (sum) costs - derived by assigning costs (£) to each relevant item in the CSRI
xxiii)	CSRI - insurance/benefit costs	Total (sum) costs - derived by assigning costs (£) to each relevant item in the CSRI
xxiv)	EuroQol	Item scores for Q1 to 5 will be weighted by utility values and summed to produce a total (this can range from −0.59 to 1, with 1 indicating full health)

Note: CDC, Centers for Disease Control; CGI, clinical global impression; CSRI, client service receipt inventory; DMEC, data monitoring and ethics committee; HADS, hospital anxiety and depression scale.

##### 

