The overall probability of falsely claiming a statistically significant result increases when multiple significance tests (or equally CIs) are interpreted simultaneously. Multiplicity considerations arise in this trial from the presence of (i) multiple outcomes, (ii) multiple intervention comparisons, and (iii) multiple analyses.

The strategy for adjusting, presenting and interpreting the results is set out below.

Multiplicity adjustments will be made as follows:

1. The following five comparisons will be made using two-sided hypothesis tests (alpha = 0.05) at 52 weeks: APT versus SSMC, CBT versus SSMC, GET versus SSMC, CBT versus APT, GET versus APT.

For the co-primary outcomes, fatigue and disability, and for the secondary outcome, the participant-rated CGI, *P*-values will be presented unadjusted for multiplicity.

2. In addition Bonferroni adjustment (0.05/5) will be applied separately to each of the three outcomes to control the outcome-wise type I error rate at 5%.

3. No adjustment will be made for any sensitivity analysis as their purpose is to increase confidence in the results obtained from the analysis nominated as primary [26].

4. No adjustment will be made within the principal paper(s) for other analyses including those for safety, secondary outcomes (except the CGI) [26], and health economics.

Presentation will occur as follows:

1. All analyses undertaken will be reported as far as practical (regardless of statistical significance) [65].

2. Estimated effects will be presented with unadjusted 2-sided 95% CIs and *P*-values.

3. *P*-values adjusted for multiplicity will also be presented and explained.

Interpretation will be done as indicated below:

1. Marginal interpretation of the results will be of primary interest and will be based on the size and precision of the observed differences between interventions with reference to point estimates and unadjusted 95% CIs.

2. Intervention recommendations will also take into consideration the consistency of effects

a. across any supportive intervention contrasts,

b. across sensitivity analyses, primary outcomes and time points,

c. across efficacy, safety and cost analyses, and

d. with the results of previous studies, and clinical and consumer opinions.

##### 

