##### **Baseline adjustment**

By design factors only

Not applicable

By design factors and additional factors

This is the primary analysis.

##### 

**Model assumption checks** The following assumptions will be checked:

1. Independence of residuals will be checked using the supportive analyses described in Method for Handling Other Clustering Effects section. ICC and within-cluster variance estimates will be reported.

2. Distribution of residuals and random effects will be checked visually using Q-Q plots and histograms of the residuals and by plotting the between-participant variation in participant outcomes and where appropriate the between-centre, the within-doctor but between-interventions, and the between-therapist variation in participant outcomes. Deviations from a Normal distribution would indicate a violation of model assumptions. In this event an alternative approach to the analysis would be investigated.

3. Equal variance of residuals will be checked visually using plots of the standardised residuals against the predicted values.

4. Absence of an intervention-by-centre interaction will be checked in the primary analysis by including fixed contrasts for the intervention-by-centre interaction.

Checks will be made for extreme outliers and points with high leverage. In the event that these are found, the analysis will be reported with and without these observations together with any relevant details.

##### 

**Other analyses supporting the primary analysis** A number of sensitivity analyses will be employed to examine the robustness of the conclusions of the primary analysis to:

1. Categorical responder/improver analysis.

Clinically significant improvement will be taken as a CGI participant score of 1 (very much improved) or 2 (much improved). CGI (P) scores of 3 (a little improved), 4 (no change) and 5 (a little worse) will be considered as non-improvement. CGI (P) scores of 6 (much worse) and 7 (very much worse) will be considered as deterioration. The primary analyses will be repeated replacing the primary outcomes with the CGI (P) (response versus no response versus deterioration) and using mixed-effects logistic regression.

2. Methods for handling missing data.

The primary analysis will be repeated assuming data are missing not at random (MNAR) as described in Method for Handling Dropouts and Missing Data section.

3. Choice of sample.

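### The participant-rated CGI is collected on seven ordered grades but collapsed to three for its ordinal model; fitting all seven would recover information at little cost

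*SAP article*

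**What the plan says.** Table 3 of the SAP, item xii, derives the participant-rated CGI as "Positive change; no change; negative change", without score cut-offs. The definition of efficacy outcomes repeats the three-category form, "Participant-, therapist- and SSMC doctor-rated CGI are defined as ordinal variables with three categories", and refers to a separate scoring protocol, which is not shown. The next sentence there treats a similar item differently: "Participant satisfaction is defined as an ordinal variable with seven categories". Both items then go into the same type of model: "Participant-rated CGI and the participant satisfaction will be analysed using mixed-effects ordinal logistic regressions".

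The seven grades appear in the section on other analyses supporting the primary analysis, item 1. For that responder analysis, scores 1 and 2 count as improvement, "CGI (P) scores of 3 (a little improved), 4 (no change) and 5 (a little worse) will be considered as non-improvement", and "CGI (P) scores of 6 (much worse) and 7 (very much worse) will be considered as deterioration".

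Secondary objective 1 asks whether the pattern of the primary results is replicated on the participant CGI. The multiplicity section gives fatigue, disability and the CGI unadjusted results for five contrasts at 52 weeks, and in addition "Bonferroni adjustment (0.05/5) will be applied separately to each of the three outcomes". The CGI is the only secondary outcome treated in this way. No seven-grade analysis of it is planned.

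**The concern.** An ordinal logistic model has no need of a collapse. Merging adjacent grades removes the ordering within each merged group, so the treatment effect is estimated less precisely from the same answers. The plan evidently accepts seven categories in this model, since satisfaction is fitted that way. An improved/not improved/deteriorated reading is already provided by the responder analysis, so collapsing the ordinal model as well does not add it.

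What is at stake is precision on the outcome chosen to show whether the fatigue and disability results are replicated. A less precise CGI estimate gives wider intervals and can make agreement with the primary outcomes look weaker than the data would allow.

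**Working it through.** **Planning figures.** For 10% v 25%, two-sided 5% and 90% power, the pooled formula gives n = [1.960 × √(2 × 0.175 × 0.825) + 1.282 × √(0.09 + 0.1875)]² / 0.15² = 133 per arm (the SAP states 135). Allowing for dropout, 135/0.9 = 150 per arm, or 600 in all, as stated. The Bonferroni level is 0.05/5 = 0.01. The SAP gives no figure for the information in the CGI.

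**Method.** Under proportional odds, with n per arm and mean category shares p_k over the two arms, the information on the log odds ratio is V = (n/6) × (1 − Σp_k³). Relative efficiency is the ratio of V for three categories to V for seven. Power = Φ(log OR × √V − z). An SD shift s is converted by log OR = s × π/√3.

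**Assumptions.** A single time point and 135 analysed per arm. The share scoring 1-2 is set to the response rates in the SAP's sample size section (SSMC 10%, APT 25%, GET 50%, CBT 60%), which were set for earlier responder outcomes. All other grade shares are assumed.

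**Worked case.** Take control shares of 3, 7, 28.3, 28.3, 28.3, 3.5 and 1.5% for grades 1 to 7, and a 0.4 SD shift. Then log OR = 0.4 × 1.814 = 0.7255 (OR 2.07), and the share scoring 1-2 rises from 10% to 18.7%. Mean shares are 4.5, 9.8, 32.9, 26.3, 22.7, 2.6 and 1.1%.

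| Form analysed | 1 − Σp³ | V | SE of log OR | Efficiency | Power at 0.01 | Power at 0.05 |
|---|---|---|---|---|---|---|
| Seven grades | 0.933 | 21.0 | 0.218 | 1 | 77% | 91% |
| 1-2/3-5/6-7 | 0.447 | 10.1 | 0.315 | 0.48 | 39% | 63% |
| 1-3/4/5-7 | 0.858 | 19.3 | 0.228 | 0.92 | 73% | 89% |

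For seven grades, for example, Φ(0.7255 × √21.0 − 2.576) = Φ(0.75) = 77%. The interval on the log odds scale is 0.315/0.218 = 1.44 times as wide under the first grouping and 1.04 times under the second.

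With 25% of controls scoring 1-2, 10% scoring 6-7 and an even middle split, efficiencies are 0.78 and 0.84, and power at 0.01 is 79% with seven grades against 66% and 70%. Over the assumed distributions examined at 0.4 SD, power at 0.01 falls from about 77-79% to about 39-66% under the first grouping and about 64-74% under the second.

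**Loss by contrast at the planning response rates.** Here SSMC deterioration was varied from 2% to 20% over seven splits of the middle grades. The power column uses 5% deterioration and an even middle split.

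| Contrast | Implied OR | Loss, 1-2/3-5/6-7 | Loss, 1-3/4/5-7 | Power at 0.01: seven grades / first / second grouping |
|---|---|---|---|---|
| APT v SSMC | 3.0 | 25-51% | 4-14% | 99 / 86 / 99% |
| GET v SSMC | 9.0 | 18-32% | 9-26% | all >99% |
| CBT v SSMC | 13.5 | 16-27% | 11-29% | all >99% |
| GET v APT | 3.0 | 19-25% | 17-46% | 99 / 97 / 92% |
| CBT v APT | 4.5 | 17-23% | 21-50% | all >99% |

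The first grouping costs most where few participants score 1-2, because most then fall in the broad 3-5 group. The second costs most where many participants improve, because they pool in 1-3.

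**The case against.** The strongest reply concerns size. A reader might infer that the plan throws away half the information in the CGI. The documents do not support that as a general statement. About half is the upper end for APT v SSMC under 1-2/3-5/6-7, and that cut is stated only for the responder sensitivity analysis. The labels in Table 3 fit 1-3/4/5-7 at least as well, and there the loss is usually smaller. This part of the reply stands.

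A reader might also infer that a true replication would be missed at the Bonferroni level. That does not follow either. The 0.3 and 0.5 SD margins in the SAP refer to fatigue and physical function, not the CGI. At the plan's own planning effects, three-category power in the case tabulated stays at about 86% or more. Bonferroni results are additional, and interpretation rests mainly on effect sizes and unadjusted 95% intervals. Nor is the three-category ordinal model stated to be the whole test of secondary objective 1: its section names objective 3, while objective 1 is assigned to the primary analysis, which the responder analysis repeats with the CGI.

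Finally, three categories are easy to read, need proportional odds across two cut-points rather than six, and avoid sparse extreme grades. These are real advantages, but a supportive three-category analysis keeps the readability, and sparse grades can be merged when they occur. The loss of precision remains in any case, because it widens the unadjusted intervals too.

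**Conclusion.** The point holds as a modest efficiency improvement on a secondary outcome. That seven grades are collected, three are analysed and satisfaction is left uncollapsed is plain from the text, and the direction of the loss is the same under both groupings. Confidence in its size is moderate: the grade distributions are assumed, proportional odds is taken to hold, and the calculation ignores the repeated measures and covariates of the planned model. The choice does not invalidate the CGI analysis. It makes it less precise than the data allow, noticeably so if effects are nearer 0.4 SD than the planning rates.

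**What to change.** In Table 3 (item xii) and in the definition of efficacy outcomes, define the participant-rated CGI as seven ordered categories, from 1 (very much improved) to 7 (very much worse). Fit the ordinal logistic model, and the five contrasts of the multiplicity section, to all seven grades. Merge adjacent grades only where one is empty or too sparse to fit. Keep the three-category version as the supportive responder analysis and for descriptive tables, with one stated set of score cut-offs so that Table 3 and the responder analysis agree.

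The cost is a change of wording and a few lines of code; no new data are needed. The downside is that proportional odds is then assumed across six cut-points and should be checked, and the extreme grades may be sparse.

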**Questionnaires**						
Chalder fatigue	✓	✓	✓	✓	✓	✓
SF-36 physical functioning	✓	✓	✓	✓	✓	✓
Participant CGI		✓	✓	✓	✓	✓
Doctor CGI				✓	✓	✓
Therapist CGI			✓		✓	✓
Walking test	✓		✓	✓	✓	
Actigraphy	✓					
HADS	✓	✓	✓	✓	✓	
Self-efficacy	✓	✓	✓	✓	✓	
WSAS	✓	✓	✓	✓	✓	
SIQ^b^	✓	✓	✓	✓		
PHQ-15	✓	✓	✓	✓	✓	
Exercise and activity	✓	✓	✓	✓	✓	
Jenkins Sleep Scale	✓	✓	✓	✓	✓	
Step test	✓	✓	✓	✓	✓	
Borg Scale	✓	✓	✓	✓	✓	
Participant satisfaction			✓	✓		
SSMC/therapy adherence			✓	✓	✓	✓
EQ-5D	✓		✓	✓	✓	
CSRI	✓		✓	✓	✓	

^a^Baseline was conducted over two research visits prior to randomisation; ^b^The SIQ is now known as the Cognitive and Behavioural Questionnaire; ^c^The therapist and doctor data will be kept separate from the trial database and summarised by the Trial Manager (see Baseline Comparability of Randomised Groups); Note: CDC, Centers for Disease Control; CGI, clinical global impression; CSRI, client service receipt inventory; EQ-5D, Euroqol 5 dimensions; HADS, hospital anxiety and depression scale; PHQ15, physical health questionnaire 15; SF-36, short-form 36; SIQ, symptoms interpretation questionnaire; SSMC, standardised specialist medical care; WSAS, work and social adjustment scale.

In addition, details were recorded for i) training sessions, ii) therapist competency, iii) quality control checks of therapy sessions, and iv) homework compliance assessments that were made after every therapy session and that will be summarized as part of the general description of intended intervention policies.

Primary and secondary outcome variables will be derived from the follow-up data at each relevant time-point as follows.

Primary outcomes:

i) Fatigue total score (Likert scoring, higher scores indicate more fatigue).

ii) Physical disability total score (sum of 10 items multiplied by 5, lower scores indicate more disability).

Secondary outcomes are presented in Table 3.

**Table 3 T3:** Derivation of secondary outcomes

	**Secondary outcome**	**Derivation**
iii)	Serious deterioration	Absent/present - derived using the DMEC algorithm
iv)	Serious deterioration: Component 1	Absent/present - SF-36 physical function score diminishing by 20 or more points between baseline and any two consecutive assessment interviews
v)	Serious deterioration: Component 2	Absent/present - Participant-rated CGI change score of ‘much worse’ or ‘very much worse’ at two consecutive assessment interviews

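### The primary CGI analysis gives one odds ratio for improvement and worsening, with no proportional-odds check, so more worsening can appear as less

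*SAP article*

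**What the plan says.** Table 3 derives participant-rated CGI as "Positive change; no change; negative change". Under Efficacy outcomes, the definition paragraph says "Participant-, therapist- and SSMC doctor-rated CGI are defined as ordinal variables with three categories". The primary analysis paragraph then states "Participant-rated CGI and the participant satisfaction will be analysed using mixed-effects ordinal logistic regressions", and adds that "The intervention and time-by-intervention contrasts fitted for the primary outcomes will be extracted for each secondary efficacy outcome".

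The model-assumption list for these outcomes opens with "The following will be checked as described for the primary analysis of the primary outcomes". Its six items are independence, distribution and equal variance of residuals, distribution of random effects, intervention-by-centre interaction, and outliers or leverage. None concerns equality of the odds ratio across the category boundaries.

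The CGI also has a safety role. Under Safety outcomes, the SAP says that the components of serious deterioration draw on the protocol's two adverse outcomes, "namely negative change on either the participant-rated CGI or the SF-36 physical function scale defined at 12, 24 and 52 weeks". The CGI component itself needs "Participant-rated CGI change score of ‘much worse’ or ‘very much worse’ at two consecutive assessment interviews". The components are tabulated by arm, and the risk-difference test is applied to the composite.

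Two other displays or analyses bear on the point. The efficacy section promises bar charts and a table by intervention and assessment point. Among the sensitivity analyses for the primary outcomes, the SAP plans to replace those outcomes with "CGI (P) (response versus no response versus deterioration) and using mixed-effects logistic regression", where deterioration means scores 6 and 7.

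**The concern.** A cumulative-logit model with proportional odds assumes that the intervention odds ratio for positive versus the rest equals that for positive or no change versus negative. For most ordinal efficacy scales a modest failure of this assumption is tolerable. Here one end of the scale is the efficacy signal and the other is a protocol-defined adverse outcome, so the assumption ties the harm estimate to the benefit estimate.

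A therapy that improves some participants and worsens others breaks the assumption. The estimate is then driven mainly by whichever boundary carries more information, usually the commoner positive category. An excess of worsening would be reported inside an odds ratio that favours therapy.

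This matters more for CGI than for other secondary outcomes. It carries secondary objective 1, and it is the only secondary outcome given a Bonferroni adjustment. The multiplicity section also bases interpretation on point estimates and 95% CIs, and no point estimate for worsening at each visit is clearly planned.

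**Working it through.** **Inputs.** The plan states no CGI category rates, so there is no plan figure to reproduce and every rate below is an assumption. Arm size comes from the SAP: 641 randomised over four arms, 641/4 ≈ 160. The fit uses expected counts at a single visit without the participant random intercept.

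**Model.** With categories ordered negative < none < positive and x = 1 for therapy, logit P(Y ≤ j) = α_j − βx. The value exp(β) is the common odds ratio for a better category, the same at both boundaries. The implied negative rate is 1/(1 + exp(−α₁ + βx)).

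**Scenario A: SSMC 10/65/25, therapy 15/45/40.**
- Odds ratio for negative change from the assumed rates: (0.15/0.85)/(0.10/0.90) = 1.59, which is harm.
- Odds ratio for positive change: (0.40/0.60)/(0.25/0.75) = 2.00, which is benefit.
- Maximum likelihood gives α₁ = −1.783, β = 0.369, SE 0.218 at 160 per arm.
- Common odds ratio: exp(0.369) = 1.45, with 95% CI exp(0.369 ± 1.96 × 0.218) = 0.94 to 2.22, P = 0.09.
- Implied negative rate on SSMC: 1/(1 + e^1.783) = 14.4%. On therapy: 1/(1 + e^2.152) = 10.4%. The assumed rates rise from 10% to 15%.

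**Scenarios at 160 per arm** (rates are negative/none/positive; SSMC v therapy):

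| Assumed rates | Common OR, better (95% CI) | Implied negative | Assumed negative | OR for negative v rest (95% CI) |
|---|---|---|---|---|
| A: 10/65/25 v 15/45/40 | 1.45 (0.94–2.22) | 14.4% → 10.4% | 10% → 15% | 1.59 (0.81–3.12) |
| B: 5/70/25 v 10/50/40 | 1.53 (0.98–2.38) | 8.9% → 6.0% | 5% → 10% | 2.11 (0.88–5.08) |
| C: 10/80/10 v 20/55/25 | 1.22 (0.77–1.94) | 16.2% → 13.6% | 10% → 20% | 2.25 (1.18–4.29) |
| D: 10/80/10 v 20/30/50 | 2.90 (1.85–4.54) | 20.3% → 8.1% | 10% → 20% | 2.25 (1.18–4.29) |

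The direction for worsening is wrong in all four. It is significant only in D. The positive rates in D match the responder rates that the sample-size section assumes for SSMC (10%) and GET (50%), although those were set for the earlier responder outcomes and not for CGI.

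**Would a check detect it?** The expected likelihood-ratio chi-square for proportional odds on 1 df is 10.2 in A, 10.1 in B, 22.8 in C and 67.1 in D, against a 5% critical value of 3.84. A check would be informative at this trial's size.

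**Does the safety analysis fill the gap?** Visits are at 12, 24 and 52 weeks. CGI worsening first reported at week 52 has no later interview to make it consecutive, so it cannot meet the CGI component. Worsening at one visit alone does not meet it either.

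**The case against.** The strongest case on the other side has five parts.

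1. **A reader might infer that CGI worsening is compared at each visit only through the ordinal model.** The SAP does not support that. The sensitivity analysis under the co-primary outcomes has deterioration as its own level, and its wording omits the word ordinal. If multinomial, it would separate harm from benefit. If ordinal, it repeats the problem; if binary, it cannot hold three levels. Its form is not stated.
2. **A reader might infer that the P-value would contradict the true direction.** In scenarios A and B it would not: P = 0.09 and 0.06, neither below 0.05 and still less below the Bonferroni level of 0.05/5 = 0.01. A significant reversal needs a large benefit and a rise in worsening together. In A and B the separate negative contrast is inconclusive too.
3. **The raw percentages are reported.** This stands. An excess of worsening would be visible by arm and visit, though without an estimate or interval.
4. **Safety has its own route.** This stands in part. The SAP says that the components of serious deterioration draw on the protocol's adverse outcomes; it does not make per-visit negative CGI a separate safety endpoint. The composite is tested and its components are tabulated.
5. **The SAP never writes proportional odds.** True. It is the usual form of ordinal logistic regression and no alternative is named, so it is an assumption here.

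**Conclusion.** The point holds for the primary CGI analysis. One odds ratio stands for both improvement and worsening, the listed checks are carried over from linear models and omit the assumption that matters, and no fallback is named. Under the assumed rates the common odds ratio runs from 1.22 to 2.90 in favour of therapy while the odds ratio for worsening runs from 1.59 to 2.25 against it.

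This rests on three assumptions: the model takes its usual proportional-odds form, improvement and worsening both rise on therapy, and the category rates are as assumed. If worsening rose without more improvement, the common odds ratio would correctly point to harm. Leaving out the random intercept changes the size of the odds ratios, not the mechanism.

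It does not follow that harm would be hidden, since the tables would show it, nor that a misleading significant result is likely. The matter is one of analysis choice, concerns no clinical management rule, and merits an amendment because it is cheap to correct.

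**What to change.** - Alongside the ordinal model, report positive versus rest and negative versus rest for each intervention contrast at 12, 24 and 52 weeks with 95% CIs. Alternatively, relax proportional odds for the intervention terms (partial proportional odds).
- Show the negative-versus-rest contrast with the safety results as well as under efficacy.
- Add a proportional-odds check for the intervention terms to the assumption list, and name the separate contrasts as the fallback if it fails.
- State the form of the three-level CGI sensitivity analysis: multinomial, or two binary contrasts.

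The cost is SAP wording and one extra set of contrasts from data already collected. The drawback is lower precision for the rarer negative category, as the wide intervals for scenarios A and B show.
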